## Methods and Analysis

The protocol follows the Standard Protocol Items: Recommendations for Interventional Trials (SPIRIT) guidelines (21).

### Study Design

Our study is a quasi-experiment with a before and after design. The interventions have both been evaluated in separate cluster RCTs (6, 22). However, our proposed studies are not conceived to be “head-to-head” comparisons of their effectiveness. The studies, rather, are *mechanism focused* and the two school-based interventions offer contrasting conditions: one leverages peer influence and the other uses a more straightforward classroom approach to deliver information. While ultimately a classroom and school based norm around smoking may change for each intervention, the change mechanism may be different.

Using a whole school year approach, our study design involves an investigation of the evolution of social networks and norms around smoking before and after a smoking prevention intervention. First, we conducted a cultural adaptation and a pilot study in three schools (one school in Northern Ireland and two schools in Colombia) with 312 pupils during 2018–2019. In 2019, in each country (Northern Ireland and Colombia) we studied ~600 pupils (aged 12–13 years/Year nine pupils in Northern Ireland and aged 12–15 years/Year seven in Colombia) in six secondary (i.e., post-primary) level schools (three receiving each intervention) exploring the contrasts between schools receiving different interventions and between countries (where norms are different).

### Interventions

The interventions were culturally adapted for use in Colombia to fit the needs of the local context while keeping their fidelity and avoiding “cultural hegemony” bias. The cultural adaptation process included four stages (information gathering, preliminary adaptation design, preliminary adaptation test, and adaptation refinement) (23). Furthermore, all the materials for data collection were translated and back translated by bilingual speakers/translators.

#### ASSIST (A Stop Smoking in Schools Trial) Intervention

The ASSIST intervention is designed to train influential pupils to use informal contacts with peers in their school year group to encourage them not to smoke (24, 25). The effectiveness of the ASSIST intervention for smoking prevention has previously been established in a cluster RCT (6). Figure 1 shows the proposed logic model depicting assumed pathways of change for participants receiving the ASSIST intervention. Underpinned by Diffusion of Innovations Theory (26), its core elements include the identification and recruitment of peer supporters (through a process of nominating pupils), who are then trained to diffuse prevention messages through informal conversations with their classmates.

**Figure 1 F1:**
[figure not shown]
Proposed logic model for the ASSIST intervention.

According to Rogers, diffusion is “the process in which an innovation is communicated through certain channels over time among the members of a social system” (26). Therefore, the four key components in the diffusion of an innovation is the innovation (e.g., smoking prevention message), communication channels (e.g., one-to-one conversations by peer supporters in their friendship groups), time (e.g., the period of time during which the message is being spread), and the social system (e.g., the school year group). The five stages of the innovation-decision process, leading to adoption (i.e., “full use of an innovation as the best course of action available”) or rejection (i.e., a decision “not to adopt an innovation”) of the smoking prevention message for each individual in the school year group are: (1) Knowledge; (2) Persuasion; (3) Decision; (4) Implementation; and (5) Confirmation. Uncertainty in adoption is reduced when individuals are well-informed about the pros and cons of adopting the message. Therefore, the communication channels (i.e., one-to-one conversations between peer supporters and their friends) are vital to progress the innovation-decision process, from the “Knowledge” stage to the “Confirmation” stage, for all members of the school year group. In the short term, it is hypothesized that the intervention will directly lead to increased knowledge regarding tobacco and its long-term health consequences for peer supporters. Therefore, peer supporters will have reduced intentions to engage in tobacco-related behaviors. During the “Knowledge” stage, peer supporters approach members of their social network (i.e., friendship groups) to convey accurate information about the risks and benefits (i.e., pros and cons) of tobacco use. During the “Persuasion” stage, early adopters and early majority (i.e., well-connected individuals who are first to receive the message), undergo a knowledge and attitude change toward tobacco-related behaviors (e.g., negative attitude toward smoking) and have increased perceptions of peer support. In the medium term, self-efficacy to quit tobacco, or remain tobacco-free, should be increased by increases in social support (i.e., vicarious experience) (27). During the “Decision” stage, early adopters, and early majority weigh up the pros and cons of adopting the message (28). Increased knowledge, attitude changes, and perceptions of peer support influence the early adopters and early majority toward implementing the innovation and reducing their smoking intentions during the “Implementation” stage (29, 30). During the “Confirmation” stage, they gain support (on-going from peer supporters) for the decision to implement the innovation. Furthermore, in the medium term, the remaining individuals in the social system (i.e., late majority and laggards) who are less well-connected than the early adopters and early majority are encouraged to undergo the same process (i.e., to progress from the “Knowledge” to the “Confirmation” stage) due to increased perceptions of peer support, changed social norms, and role modeling (27, 31). In the longer-term, the intervention is expected to lead to reduced rates of initiation of tobacco-related behaviors, delayed average age at first tobacco-use, reduced morbidity and mortality, and improved health and mental well-being (32–35).

According to the Diffusion of Innovations Theory, contextual factors influencing the rate of adoption include: relative advantage (i.e., the degree to which an innovation is perceived as being better than the preceding idea); compatibility (i.e., the degree to which an innovation is perceived as being consistent with existing values, experiences and needs of adopters); complexity (i.e., the degree to which the innovation is perceived as being difficult to understand and use); trialability (i.e., the degree to which an innovation may be experimented with on a limited basis); and observability (i.e., the degree to which the results of the innovation are observable to others via role modeling for example) (27, 36).

All pupils in participating schools are asked to complete a peer questionnaire to nominate up to five pupils they view as influential in different respects (i.e., whom they respect, who they think are good leaders in sports or other group activities, whom they look up to) in their year at their school. The top 18% nominated pupils in each year group are invited to train and take on the role of “peer supporter.” The intervention provides peer supporters with the knowledge and skills necessary to spread information about the harms of tobacco-use amongst the remaining members of the school year group (i.e., peer education and diffusion).

Broadly, the 2-days peer supporter training course aims to increase knowledge about the health, economic, social, and environmental risks of smoking; emphasize the benefits of remaining smoke-free; and encourage the development of skills to enable peer supporters to promote non-smoking among their peers. The training program consists of three broad categories of information giving, communication skills, and personal development. After the peer supporter training, peer supporters intervene informally in everyday situations over a 10-weeks period to encourage their peers not to smoke, and to keep a diary record of these informal conversations. Trainers make four follow-up visits to each school over this 10-weeks period to provide further training to the peer supporters and to monitor their progress. The detailed protocol for the ASSIST intervention was developed by Evidence to Impact (http://evidencetoimpact.com/), a social enterprise. The developers of ASSIST visited Bogotá in order to assess fidelity of the intervention.

#### Dead Cool Intervention

Dead Cool is a smoking prevention intervention for pupils aged 12–13 years old designed by Cancer Focus Northern Ireland (a local cancer charity) (22, 37). The intervention is designed to be delivered by teachers and consists of eight lesson plans and an accompanying DVD of short video clips to supplement each lesson. The intervention aims to reduce the number of young people who start smoking and to examine the influences on smoking behavior from friends, parents, other family members, and the media. Teachers from the school deliver the intervention in their own classes over an 8-weeks period. The lessons last for ~20–30 min. Teachers have a Teachers' Resource Pack and pupils have a Pupil Workbook that contains exercises for each lesson. Before the start of the intervention, pupils have an introductory session to the intervention and teachers receive professional development that outlines the focus and epistemology behind the product design.

Figure 2 shows the proposed logic model depicting assumed pathways of change for participants in the Dead Cool intervention. The intervention is motivated by more conventional classroom pedagogy and the Theory of Planned Behavior (29, 30). The theory has elsewhere been tested and evidence suggests that it delays or prevents smoking initiation (38). The intervention includes a range of behavior change techniques (BCTs) including provision of information about consequences, information about behavioral antecedents (e.g., influence from friends, family, and the media), problem solving, and social support. In the short-term it is hypothesized that the intervention's information provision components should lead directly to increased knowledge about tobacco and the long-term health consequences, with emphasis on the salience of outcomes leading to fear arousal and anticipated regret (39, 40). Provision of normative information regarding the prevalence of smoking and tobacco related behaviors for the participants' age group should reduce “misperceptions” and act to align perceived social (descriptive) norms with actual norms (41–43). The intervention should lead to increased awareness of the sources of support available and of how to seek support from family and friends. Self-efficacy to quit tobacco, or remain tobacco-free, should be increased by increases in social support (i.e., vicarious experience) (27). In the medium term, increases in perceived social support from family and peers, changing attitudes toward tobacco-related behaviors (e.g., negative attitude toward smoking) and changes in perceived social norms should lead participants to form intentions not to smoke or engage in tobacco-related behaviors (29, 30). In the longer-term, the intervention is expected to lead to reduced rates of initiation of tobacco-related behaviors, delayed average age at first tobacco-use, reduced morbidity, and mortality, and improved health and mental well-being (32–35).

**Figure 2 F2:**
[figure not shown]
Proposed logic model for Dead Cool intervention.

In a pilot cRCT (37) in 18 schools (20 classes, 399 pupils, Year 9), Dead Cool was effective at reducing smoking susceptibility and carbon monoxide (CO) validated smoking behavior; (standardized effect size 0.38). However, there was unexplained school level heterogeneity in the effects (22). It has been proposed that social norms and peer influences may moderate some of the effects of such interventions (44). However, the Dead Cool intervention does not specifically train peer supporters to deliver prevention messages in the way that the ASSIST intervention does. The developers of Dead Cool visited Bogotá in order to assess fidelity of the intervention.

This team conducted an independent observational study of schools in Northern Ireland (*n* = 17) (Belfast Youth Development Survey). We employed the same actor-based hidden Markov models as Steglich et al. (7) and were able to demonstrate distinct school level heterogeneity in the effects of social networks on smoking behavior (45). Thus, both the ASSIST and Dead Cool studies suggest that local contextual factors might moderate or mediate some of their effects.

#### Intervention Delivery and Fidelity Checking

The ASSIST intervention was delivered by health promotion trainers from the local public health agency in respective countries who had participated in the ASSIST “Train the Trainer” sessions which enabled them to deliver the intervention in a standardized manner (6, 25). This is a 3-days session delivered by Evidence to Impact. The Dead Cool intervention was delivered by teachers in participating schools with an introductory session delivered by a Cancer Focus Northern Ireland employee (22, 37). In Bogotá, Dead Cool was delivered by trainers from the Universidad de Los Andes. Prior to the intervention, teachers in Northern Ireland received ~120 min of professional development. The teachers from Bogotá received a 2-days workshop (16 h) on professional development.

Up to three of the training and intervention sessions in Bogotá were video-taped to check intervention fidelity. The audio of the video tapes was transcribed and translated to English to enable project partners at Cancer Focus Northern Ireland and Evidence to Impact (who developed the interventions) to check for intervention fidelity. The translated transcripts were viewed alongside the video tape. Intervention fidelity and delivery were assessed by collecting data from trainers and teachers implementing the Peer Supporter Training and Follow-Up sessions. Fidelity checks include: pupil attendance, activity coverage, activity completed, lesson cover, lessons completed, content covered, and use of extension activities.

### Recruitment

#### Recruitment of Schools

Six post-primary schools were recruited in Northern Ireland and six in Bogotá during 2019. In Northern Ireland, schools were selected to ensure a mix of State and Catholic maintained schools, with some serving urban and rural catchments, and maximum variation sampling to ensure schools with high and low proportions of pupils eligible for free school meals. In Bogotá, six public schools from low to middle socio-economic status with maximum variation by geographic location were selected.

In Northern Ireland, relevant schools were identified from the database of schools which have previously been involved in research with the Center for Public Health and School of Education (currently over 200 schools in Northern Ireland). Schools were selected based on the sampling framework highlighted above. Schools identified as eligible were sent a letter (addressed to the school Principal or relevant senior member of staff) outlining the purpose of the study and inviting them to take part. A follow-up phone call by a member of the research team, ~1 week after delivery of the invitation letter, provided further details and an opportunity to answer any questions. For those schools agreeing to take part, a study pack was delivered providing further details about the study and role of the school.

In Bogotá, the sampling of schools followed these steps. First, a list of 40 private and public schools were prioritized based on health risks by the Education and Health Departments of Bogotá. Second, from this list, 13 schools were invited to participate according to the following inclusion criteria: (1) schools in an urban area; (2) including boys and girls; (3) having an enrollment of between 90 and 150 students in 7th year. Third, only six schools accepted the invitation and were selected for the final sample. These schools were assigned randomly to each of the interventions. Three schools were assigned to the ASSIST (*Entre Parceros*) intervention, and the other three were assigned to the Dead Cool (*Bacan*í*simo*) intervention. Schools identified as eligible were visited multiple times and researchers presented the outline of the study to the school Principal and to relevant members of staff, and invited them to take part. For those schools agreeing to take part, a study pack was delivered providing further details about the study and role of the school.

#### Recruitment of Participants

For each school recruited, we aimed to recruit all classes in a single year group (~*N* = 80–100 on average per school; study *N* = ~600 for each country). In each school, we targeted Year 9 pupils in Northern Ireland and Year 7 in Bogotá, who were 12–13 years old. All pupils in the school year were invited to participate. Prior to the conduct of the Game Theory Experiments, each school was given Teacher Information Sheets, Pupil Information Sheets, Parent/Guardian Information Sheets, Pupil Consent Forms, and Parent/Guardian Opt-Out Forms (providing information about the study). All pupils were required to complete Consent Forms indicating whether they agree or decline to participate. In Northern Ireland, Parents/Guardians who did not wish their child to take part were asked to return completed Opt-Out Forms.

### Sample Size

As this is a proof of concept study, we have provided an exemplar power calculation to assess how the social network clustering of smoking-related social norms might change after a prevention intervention (${\text{H}}_{0}^{5}$). This draws on the work of Krupka who studied ~200 Michigan university freshmen before and after a single semester. Krupka did not have data on smoking *per se* among the freshmen, but did have their elicited time and risk preferences. These measures of preferences are more fundamental behavioral economic traits that are correlated with smoking behaviors (46). Using the basic Clauset et al. community detection algorithm (47), with a sample size of ~200, and with data from two waves, Krupka found that a one standard deviation (*SD*) increase in risk preferences of an individual's friends or social network is associated with an increase of 1/8 to 1/10th of a SD (of the same variable) for the individual. Assuming that clustering of risk preferences is a reasonable proxy for clustering of social norms related to smoking that we will elicit, we estimate that a sample size of 300 would give over 80% power to detect, as statistically significant at the 5% level, a slope of 0.16. In other words, an increase of 0.16 *SD*s in individual norms sensitivity, per *SD* increase in norms sensitivity of those in the individual's social network.

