How are individual psychosocial and cognitive traits at baseline related to individual sensitivity to social norms? (**H**_**0**_^**1**^: that they are independent);How does individual sensitivity to social norms cluster among friendship cliques and across school year groups? (**H**_**0**_^**2**^: that the individual social norms sensitivities among friendship cliques are un-correlated);How are average social norms, measured at the classroom and year group level, affected by social network structures? (**H**_**0**_^**3**^: that social norms and social network structures are independent);After each intervention: how are changes in attitudes, intentions and behaviors toward smoking related to social norms sensitivity at the individual level, and to average social norms at the class and year group level? (**H**_**0**_^**4**^: that the changes in smoking related attitudes, intentions, and behaviors are independent of norm-sensitivity at the individual level and the same in schools which offered each intervention);After each intervention: have smoking-related social norms changed and how are these changes correlated among friendship cliques? (**H**_**0**_^**5**^: that any changes in social norms are independent among members of the same friendship clique; we assume that there will be little change in measures of homophily across one semester).

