
##### Social networks and pro-sociality

At baseline and 1 week after the end of the intervention period, pupils were asked questions about social networks in their year group (i.e., closest school friends (37), relationship quality, friends who he/she spends most time with outside of school, influential peers) (24). The following final question was added only at follow-up “Can you remember having any conversations with your friends about the risks and benefits of smoking over the past 6 months? If so, how many and with whom?” Pupils were provided with a school year roster in order to help with completion of the social network nominations. Pro-sociality will be assessed with the Need to Belong Scale (62), Fear of Negative Evaluation Scale (63, 64), and Pro-Social Behavior Scale (65).

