### Statistical Methods

#### Elicitation of Social Norms and Social Network Analyses

Injunctive social norms will be modeled quantitatively, such that a decision maker's “pay-off” u(a_k_) from a set of actions V {π(a_k_)} is related to the parameter γ ≥ 0, representing the degree to which the individual cares about adhering to social norms, in: u(a_k_) = V {π(a_k_)} + γN(a_k_), with the function N capturing the social norm, [i.e., the social appropriateness of action a_k_ denoted by N(a_k_)]. We let N_g_(a_k_) denote the social norms for group *g*, estimated from the Coordination games. γ is the key parameter reflecting individual sensitivity to the norm, estimated using the total number of balls allocated to the blue “rule following” bucket in the RF task. The Dictator and Coordination games allow us to identify norms related to prosocial behavior and to smoking related activities in the target population. We can then explore whether the norms related to smoking actually do change and whether data from the RF experiments help us predict who is more sensitive to following those changed norms after the intervention. We will also measure correlations (Spearman's rank correlation) between an individual's norms-sensitivity parameter and his/her decisions in the Donation game. We will use tobit regressions that allow for censoring, regressing the distance (Δ_SNdist_) between an individual's choice and the observed average norm (average Dictator choice) in the relevant reference group on his/her norm-sensitivity parameter. The tobit regression allows us to see if there is a statistically significant relationship between norm-sensitivity and the changed norms after the intervention. We will use similar techniques when examining social norms related to tobacco use and individuals' abilities to identify them in the Coordination game. For each behavioral vignette (whose appropriateness is rated), we will calculate a correlation between individuals' norms-sensitivity parameters, and their chosen score on the social appropriateness scale, after calculating (Δ_SNdist_). Scores on the appropriateness scale are categorical, requiring ordered probit regressions. We will conduct the above analysis both pre- and post-intervention but since we will have two observations for each individual, we will use the respective panel random effects versions (including a dummy variable to identify post-intervention observations). In all regressions, we will calculate standard errors clustered on school classes. We will account for individual participants' demographic and psychosocial characteristics, and dummy variables signifying intervention type (ASSIST or Dead Cool intervention) and country (Colombia or Northern Ireland).

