
${\text{H}}_{0}^{1}$**: that individual psychosocial traits and susceptibility to social norms are independent**: After checking distributional assumptions, multiple linear regression (and where appropriate analysis of variance; ANOVA) will be employed, with any necessary transformations of raw variables; a sample size of 600 in each country achieves 80% power to detect a correlation coefficient of 0.16 for the association between susceptibility to social norms and a continuous psychosocial trait, after adjusting for a design effect of 1.99, assuming a sample of 100 per school and intra-class correlation coefficient (ICC) = 0.01.

${\text{H}}_{0}^{2}$**: that the individual social norms susceptibilities among friendship cliques are uncorrelated**: the analytic approach in this case will be similar to that for ${\text{H}}_{0}^{5}$ which is illustrated in the section sample size for the purpose of power calculation.

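### The power statement for the friend-clustering slope (H5, and H2 by reference) treats 300 pupils as independent pairs; with reciprocated friendships, power at 300 is about 50–65%, not over 80%

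*Protocol article*

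**What the plan says.** The Sample Size section gives one exemplar calculation, for H5: "a sample size of 300 would give over 80% power to detect, as statistically significant at the 5% level, a slope of 0.16". It explains the slope as "an increase of 0.16 *SD*s in individual norms sensitivity, per *SD* increase in norms sensitivity of those in the individual's social network", so the same variable stands on both sides of the regression. No design effect or allowance for network dependence is mentioned there.

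The research questions state the H5 null as "that any changes in social norms are independent among members of the same friendship clique; we assume that there will be little change". In the section on elicitation of social norms and social network analyses, H5 is referred back to Sample Size, and for H2 "the analytic approach in this case will be similar to that for" H5. That section also says: "In all regressions, we will calculate standard errors clustered on school classes".

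Under Recruitment of Participants, all classes of one year group are targeted in each school, about 80–100 pupils. Under Social networks and pro-sociality, the network questions concern the pupil's year group, and "Pupils were provided with a school year roster in order to help with completion of the social network nominations". Friends can therefore be named from any class in the year.

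**The concern.** When a pupil's value is regressed on the mean of friends' values, and friends belong to the same recruited year group, a mutual friendship enters the data twice with the roles swapped. The rows are then dependent even if pupils' values are fully independent and classmates share no exposure. A standard error for independent pairs is too small.

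Two things follow. The planned sample delivers less power than stated for the peer-clustering question, which is central to a study of how norms spread. A test that does not allow for the dependence also rejects too often when the H5 or H2 null is true. The second consequence depends on how far the planned class-clustered errors absorb the dependence, so the two are kept apart below.

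**Working it through.** **Inputs from the article.** n = 300, standardised slope 0.16, 5% level (taken as two-sided; the article does not say), power over 80%; class-clustered errors in all regressions; about 600 pupils per country.

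**Inputs assumed.** Share of reciprocated ties r between 0.4 and 1, clique size 4–12, and whether cliques lie within or across classes. The article gives none of these. Own and friends' values are taken as measured at the same time, or both as changes.

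**Step 1: reproduce the stated figure.** With 300 independent pairs the standard error of a standardised slope is 1/√300 = 0.0577. Then 0.16/0.0577 = 2.771, and power = Φ(2.771 − 1.96) = Φ(0.811) = 79.1%. Fisher's z gives 79.4%, the noncentral t 79.9%, and a residual SD of √(1 − 0.16²) gives 80.2%. The stated figure is that of 300 independent pairs.

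**Step 2: variance with reciprocated ties.** Let y be independent standardised values and W the row-normalised tie matrix with k friends per pupil. The numerator of the slope is y′Wy, and

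Var(y′Wy) = tr(WW′) + tr(WW) = (n/k)(1 + r).

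The second trace counts ties that run both ways; independent pairs would lack it. The variance of the standardised slope is therefore (1 + r)/n instead of 1/n. In a clique every tie is mutual, so r = 1.

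**Step 3: power at slope 0.16 with a valid null.** Power ≈ Φ(0.16·√(n/(1+r)) − 1.96).

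| n | r | SE of slope | 0.16/SE | Power |
|---|---|---|---|---|
| 300 | 0 | 0.0577 | 2.771 | 79% |
| 300 | 0.4 | 0.0683 | 2.342 | 65% |
| 300 | 1 | 0.0816 | 1.960 | 50% |
| 600 | 1 | 0.0577 | 2.771 | 79% |

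Simulation (20,000 data sets, leave-one-out clique mean, cliques of 4, 6 and 10, critical values from the simulated null) agrees: 51–53% at 300 pupils and 80–81% at 600.

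**Step 4: size of a 5% test.** For a test that assumes independent pairs, two-sided size = 2·[1 − Φ(1.96/√(1+r))]: 9.8% at r = 0.4 and 16.6% at r = 1. Simulated cliques gave 16–19%.

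That is not the planned test. With class-clustered errors and t critical values, simulation gave:

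- cliques wholly within classes: about 6%;
- individual nominations with 40–100% of friends in class: about 5–10%;
- cliques crossing classes: about 12–15%, of which the upper tail (positive clustering) is 5–6% against 2.5% nominal.

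The upper tail is the smaller part because excluding the pupil's own value biases the slope slightly downward under the null.

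**The case against.** **The article already plans class-clustered errors.** This stands in part. A reader might infer from Step 4 that the planned 5% test rejects at two to three times its nominal rate. The article does not support that as a general statement: the higher rates belong to an unclustered test, which it does not specify. With the planned errors, such a rate arises only where cliques cross classes. The year-group roster allows this, but nothing shows how common it is.

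**Reciprocity and the regression form are assumed.** This stands as a condition. At r = 0 there is no inflation. If own follow-up were regressed on friends' baseline values, the inflation would be 1 + ρ²r, with ρ the correlation of a pupil's baseline and follow-up values, which is smaller. But H5 concerns changes within cliques and H2 concerns sensitivities within cliques; both suggest values from the same time and largely mutual ties.

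**300 may already be an effective sample size.** For H1 the article uses a design effect of 1.99 with the same 0.16, and 600/1.99 = 301.5. Sample Size does not say that 300 arose this way, and that design effect is for school clustering (1 + 99 × 0.01 = 1.99), not for reciprocated ties.

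**The study has about 600 pupils per country.** This stands and softens the consequence: if H5 is tested on a whole country, power is close to 80% even at r = 1. The stated calculation is nonetheless for 300.

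**The exact inference may be left to an analysis plan.** This is fair for the p-value procedure, so the absence of a named permutation test is not the finding. The power figure is in the article itself.

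**Conclusion.** The power statement for H5, which also serves as the model for H2, does not hold as written. It is the power of 300 independent pairs. When own and friends' values are measured at the same time and 40–100% of ties are reciprocated (assumed), power for a slope of 0.16 at 300 pupils is about 65% down to 50%. About 600 pupils give roughly 80% when all ties are mutual.

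The effect on the error rate is conditional. With the planned class-clustered errors the 5% test is near nominal, about 6%, if friends share a class, and about 12–15% two-sided if cliques cross classes. The documents do not support a general claim that it rejects two to three times too often.

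The variance formula is secure. The size of the effect rests on reciprocity and clique structure, which the pilot networks could supply. The point is worth correcting before analysis but does not call the design into question.

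**What to change.** 1. Restate the power in Sample Size allowing for reciprocated ties, either by simulation on the friendship networks from the pilot (312 pupils in three schools) or for the roughly 600 pupils per country. State the assumed reciprocity, whether friends' values are baseline, follow-up or change, and how this relates to the class-clustered errors.
2. Take the p-value for H2 and H5 from a permutation that keeps the observed ties and preserves class structure: permute values within class, or permute class-adjusted values. Leave the pupil's own value out of the friend mean.

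Free permutation within school should be avoided. It breaks the class structure and would reject on shared class exposure alone: with an assumed class ICC of 0.05 and no peer effect, it rejected in 10–44% of simulated data sets.

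Cost: the stated power becomes less favourable and the analysis needs slightly more work. No extra pupils are needed if the claim is restated for the sample already planned.
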